### 8.4. Frequency and Plans for Auditing Trial Conduct

A monitor from the Ethical Scientific Committee of the Universidad de los Andes will check once a year the presence and completeness of the investigation files such as informed consents, inclusion and exclusion criteria, and data collection and storage.

### 8.5. Plans for Communicating Important Protocol Amendments to Relevant Parties (e.g., Trial Participants, Ethical Committees)

All substantial amendments will be notified to the Ethics Committee of the Universidad de Talca. In case amendments concern or affect participants in any way, they will be informed about the changes. If needed, additional consent will be requested and registered. Additionally, online trial registries will be updated accordingly.

### 8.6. Dissemination Plans

The results of this research will be disclosed completely in international peer-reviewed journals. Both positive and negative results will be reported. An executive summary of the results will be given to school authorities.

## 9. Discussion

This study is the first in Latin America to test the effectiveness of a blended school-based intervention to reduce suicidal ideation among adolescents in a cluster randomized controlled trial (cRCT). The whole intervention proposed in this protocol was based on the promissory results of the internet-based component (Reframe-It) and the evidence showing the need to include face-to-face therapeutic sessions. If the effects of the intervention are positive, wide implementation in Chile and other Latino American countries could be possible in the future.

This project faces several challenges related to feasibility and the implementation to be addressed in order to help the scaling-up process in the future. For instance, this project requires a large sample size, which implies on the one hand a high demand in time and effort for the research team and on the other hand a high degree of motivation and involvement from the schools. Regarding the latter, sometimes it is not easy for the schools to accept the degree of commitment and workload needed to conduct this kind of project. To minimize these risks, we will prepare the recruitment and the training for the schools carefully and inform them in good time of all the steps and milestones of the project.

## 10. Conclusions

We expect to test the effectiveness of a blended CBT intervention to reduce suicidal ideation in adolescents as the primary outcome. Moreover, we expect to provide evidence on the potential mediation role of hopelessness, emotional regulation, and problem-solving skills on the effect of the intervention to reduce suicidal ideation.

## Figures and Tables

**Figure 1 ijerph-19-03947-f001:**
[figure not shown]
Conceptual model of mediation.

**Table 1 ijerph-19-03947-t001:** Standard Protocol Items: recommendations for International Trials (SPIRIT) diagram.

	STUDY PERIOD																			
TIMEPOINT	2022						2023											2024		
	Enrolment				Allocation		Post-Allocation											Follow-Up		Close-Out
	Aug.	Sep.	Oct.	Nov.	Dec.	Jan.	Feb.	Mar.	Apr.	May.	Jun.	Jul.	Aug.	Sep.	Oct.	Nov.	Dec.	Mar.	Sep.	Oct.
**ENROLMENT**																				
Contact with schools	X	X	X	X																
Eligibility screen			X	X	X															
Allocation					X															
Schools are informed about group belonging					X	X														
Informed consent								X												

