### 2.2. Recruitment and Informed Consent

The schools will learn about the study through invitations made to their institutional email and social networks. Eligible schools will be invited to participate through letters sent to the authorities, who will sign an agreement letter to participate in the study. This research project has the approval of the Scientific Ethics Committee of the Universidad de Talca (12 May 2021). At the beginning of the academic year, we will send a letter to the emails with information about the study, inclusion and exclusion criteria, screening instruments, the selection process, and the written consent to all parents or main caregivers of students. The informed and written consent will be signed digitally through Qualtrics. Qualtrics is a platform that allows information to be collected online with high security standards and that also can facilitate the digital signature through a cell phone or tablet (using the finger) or through a computer (with a mouse). Additionally, all students attending grades 9–11 of selected schools will be invited to participate through informative talks about the study. All students will be asked for written assent. All consented/assented students will be surveyed with the following screening questionnaires during the second month of the academic year: the Columbia Suicide Severity Rating Scale (C-SSRS) [58]; PHQ-9 [61]; and the Community Assessment of Psychic Experiences-Positive (CAPE-P15) [59]. The Qualtrics platform will also be used to collect data of screening instruments: suicidal ideation (SI) and suicide attempts (C-SSRS), depressive symptoms (PHQ-9), and psychotic symptoms (CAPE-P15). These data will be used for the study eligibility analysis. All who report any level of SI during the previous month (score ≥ 3 in the C-SSR) will be invited to participate in the following step of the study. Informed consent will cover general screening, baseline measurements, and follow-up during and after the intervention.

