### 3.6. Outcomes

Self-report questionnaires assessing primary and secondary outcomes will be administered at baseline (one week before the start of the intervention), at post-intervention, and follow-up (3, 6 and 12 months). Primary and secondary outcomes will be measured electronically using Qualtrics.

Participants will be asked sociodemographic information including, age, sex at birth, gender, race/ethnicity, education, family income, and psychological/psychiatric treatment.

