## 4. Assignment of Interventions: Allocation

Randomization will be performed once all schools are recruited. Schools will be randomly assigned to either group with a 1:1 allocation as per computer-generated randomization. In order to reduce the risk of allocation bias, the size of the schools and the vulnerability index will be taken into account to balance the groups. 

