### 4.2. Concealment Mechanism

After the randomization and allocation, schools will be informed by a research assistant of the group of belonging by email and confirmed by telephone. Each school will only receive their information of allocation. Additionally, this information will not be disclosed to the assessment research team (outcome evaluators) to keep the blind to the school allocation.

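### Schools learn their arm two to three months before families consent, and nobody involved in recruitment is blinded, so who enrols can differ by known arm

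*Protocol article*

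**What the plan says.** **Randomisation and disclosure.** Section 4 states: "Randomization will be performed once all schools are recruited". Section 4.2 continues: "After the randomization and allocation, schools will be informed by a research assistant of the group of belonging by email and confirmed by telephone". No school is told any result but its own, and the allocation is withheld from the outcome evaluators. Under section 4.3 an independent statistician randomises and passes the list to a research assistant, who informs the schools. In Table 1, allocation is in December 2022 and the row "Schools are informed about group belonging" spans December 2022 and January 2023.

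**Recruitment of students.** Section 2.2 begins: "At the beginning of the academic year, we will send a letter to the emails with information about the study". The letter goes to all parents or main caregivers, and consent is signed digitally. Students in grades 9 to 11 are invited through talks and asked for assent. Then: "All consented/assented students will be surveyed with the following screening questionnaires during the second month of the academic year". Table 1 has "Informed consent" in March 2023, baseline in May and the blended intervention from June to September. Section 3.6 places baseline a week ahead of the intervention.

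**Who is blinded.** Sections 5.1 and 5.2 blind outcome assessors and data analysts. Section 5.2 calls the design open-label and says that participants know their group. Section 8.1 gives the collection of consents to research assistants, the same role that announces the allocation.

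**Screening row.** Table 1 has "Eligibility screen" in October to December 2022 and does not say whether schools or students are meant.

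**The concern.** Randomising schools makes the schools comparable. It makes the students comparable only if enrolment does not depend on the arm. When students are recruited after the arm is known, a difference between arms can arise from who agrees to take part and from what they disclose, and not only from the intervention.

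Entry here has several steps that could respond to a known arm: parental consent, student assent, and self-reported answers on ideation, recent attempts, depression and psychotic experiences (section 2.1). Training also falls in March 2023, the month of consent, so preparation may be visible in intervention schools while families are deciding. At stake is the comparability of the arms on the primary outcome, self-reported suicidal ideation. Intention-to-treat analysis protects comparability after enrolment and cannot restore what was lost at enrolment.

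**Working it through.** **1. Order of events**

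| Event | Date | Source |
|---|---|---|
| Contact with schools | Aug to Nov 2022 | Table 1 |
| Eligibility screen (unit not stated) | Oct to Dec 2022 | Table 1 |
| Allocation | Dec 2022 | Table 1; section 4 |
| Schools told their arm | Dec 2022 to Jan 2023 | Table 1; section 4.2 |
| Family consent; training | Mar 2023 | Table 1; section 2.2 for consent |
| Student screening | about Apr 2023 | section 2.2, if the March consent marks the start of the school year |
| Baseline | May 2023 | Table 1 |
| Intervention | Jun to Sep 2023 | Table 1 |

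Disclosure therefore precedes consent by 2 to 3 months, student screening by about 3 to 4, and baseline by 4 to 5.

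**2. Does the screening row change this?** If it means schools, the table and section 2.2 agree. If it means students, it conflicts with section 2.2, where only consented and assented students are screened. Consent and baseline follow disclosure on either reading.

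**3. Is anyone in recruitment unaware of the arm?** Sections 4.2, 5.1 and 5.2 name outcome evaluators and analysts. No section says that recruiting staff, schools, families or students are unaware of the arm at consent or screening.

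**4. Illustrative size.** The plan gives no figure to reproduce here. Inputs from the document:

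- 10 schools per arm (section 2.1)
- 14 students per school and 20% loss (section 3.8)
- an effect of 0.4 SD (section 3.8)

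Assumptions:

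- enrolment shift between arms of 0.1 or 0.2 SD
- baseline-outcome correlation 0.5
- ICC from 0 to 0.05
- no baseline adjustment
- no true effect
- normal reference distribution, two-sided 5% test

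Bias = shift × correlation:

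- 0.1 × 0.5 = 0.05 SD, and 0.05 / 0.4 = 12.5%
- 0.2 × 0.5 = 0.10 SD, and 0.10 / 0.4 = 25%

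Students analysed per school: m = 14 × 0.8 = 11.2. Per arm: n = 10 × 11.2 = 112.

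SE = √(2[1 + (m − 1) × ICC] / n):

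- ICC 0: √(2 / 112) = 0.134
- ICC 0.05: √(2 × 1.51 / 112) = 0.164

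Rejection rate = 1 − Φ(1.96 − bias/SE) + Φ(−1.96 − bias/SE):

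| Bias | ICC 0 | ICC 0.02 | ICC 0.05 |
|---|---|---|---|
| 0.05 SD | 6.6% | 6.3% | 6.1% |
| 0.10 SD | 11.6% | 10.5% | 9.3% |

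The nominal 5% becomes about 6% to 7% for the smaller shift and 9% to 12% for the larger.

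**The case against.** The case for the plan has substance.

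- **School-level concealment is sound.** An independent statistician randomises, and only once all schools are in.
- **Staff have little room to pick students.** A reader might infer that school staff who know the arm choose who enters. The documents do not support that. The study team writes to all parents, every student in the grades is invited, consent is digital and eligibility rests on self-report questionnaires.
- **Control families are not offered nothing.** Usual care includes assisted referral and psychologist assessment, with psychotherapy among the possible courses (section 3.1). Parents also consent before knowing whether their child qualifies. That control families would see little reason to join is conjecture.
- **Severity is measured at baseline.** Section 7.1 compares change from baseline, so measured differences in ideation are at least partly handled. Carrying a whole 0.1 to 0.2 SD shift into the outcome, which would be 25% to 50% of 0.4 SD, overstates the bias under the assumptions above.
- **The screening row may refer to schools.** It follows the row on contact with schools, and section 2.2 speaks of schools as eligible. Reading it as proof that students are screened before consent goes too far.

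These points narrow the concern without closing it. Universal invitation and online forms prevent hand-picking, but they do not make consent, assent or candour independent of a known arm. Baseline adjustment cannot reach unmeasured factors such as motivation. The article does not say that the consent letter names the arm, but it does not prevent it either.

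**Conclusion.** The order of events is stated in both the text and Table 1: disclosure to schools comes before family consent, student screening (by section 2.2) and baseline, and no blinding of recruitment is described. This leaves a real and avoidable risk of differential enrolment.

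A reader might go further and infer that the randomisation is undone or that the arms will differ. The documents show a risk, not an occurrence, and give no consent or eligibility rates from which to judge it. The 0.05 to 0.10 SD bias, and the rejection rates of about 6% to 12%, rest wholly on the assumed shift, correlation and ICC and on the absence of baseline adjustment. They indicate scale only. Baseline adjustment would reduce the part due to measured severity; any part due to unmeasured differences would remain.

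**What to change.** 1. Keep the allocation list with the independent statistician. Disclose it to schools, families and recruiting staff only after consent, screening and baseline have closed in the schools. Amend sections 4.2 and 4.3 and Table 1 to match.
2. Move arm-specific training from March to after disclosure, and close baseline early enough to leave room for it.
3. If this is not feasible, have existing research assistants who do not know the arm handle consent and screening, using materials with the same wording in both arms. This is weaker, because schools and possibly families would still know.
4. Label the "Eligibility screen" row of Table 1 as schools or students. If it means students, reconcile it with section 2.2.

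Cost: the main change needs no extra participants or staff, but it is more than a change of dates. Section 3.6 leaves one week between baseline and the intervention, and section 3.2.1 requires a trained psychologist in each school that delivers the programme. Either the training window tightens or that gap grows. Schools would also have shorter notice of their arm, which matters given the workload concerns raised in section 9.

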**INTERVENTIONS**																				
Training								X												
Blended intervention											X	X	X	X						
**ASSESSMENTS**																				
**Baseline variables** (descriptive features, suicide ideation, suicide attempts, anxiety, hopelessness, social problem and cognitive-behavioral skills, emotional regulation)										X										
**Outcome variables** (suicide ideation, suicide attempts, anxiety, hopelessness, social problem and cognitive-behavioral skills, emotional regulation)														X			X	X	X	X
**DISSE** **MINATION**																	X	X	X	X

X = milestone.

## Data Availability

Not applicable.
